#### **8.1.5.2. New onset of neurological diseases**

New onset of neurological diseases will be reported as AEs/SAEs in the eCRF or SAE Report screens, as applicable.

### **8.2. Events or outcomes not qualifying as adverse events or serious adverse events**

#### **8.2.1. Pregnancy**

Any female subjects that are pregnant or lactating at the time of vaccination must not receive additional doses of study vaccines and must not be challenged with parasitized mosquitoes but may continue other study procedures at the discretion of the investigator.

While pregnancy itself is not considered an AE or SAE, any pregnancy complication or elective termination of a pregnancy for medical reasons will be recorded as an AE or a SAE, as described in Section 8.1.1 and 8.1.2, and will be followed as described in Section 8.5.

A spontaneous abortion is always considered to be a SAE and will be reported as described in Section 8.4. Furthermore, any SAE occurring as a result of a post-study pregnancy AND considered by the investigator to be reasonably related in time to the receipt of the investigational product will be reported to GSK Biologicals and MVI as described in Section 8.4. While the investigator is not obligated to actively seek this information from former study participants, he/she may learn of a pregnancy through spontaneous reporting.

### **8.3. Detecting and recording adverse events, serious adverse events and pregnancies**

#### **8.3.1. Time period for detecting and recording adverse events, serious adverse events and pregnancies**

All AEs starting at the first receipt of study vaccine up to 30 days following sporozoite challenge must be recorded into the Adverse Event screen in the subject's eCRF, irrespective of intensity or whether or not they are considered vaccination-related.

The standard time period for collecting and recording SAEs will begin at the first receipt of study vaccines and will end 180 days (approximately 6 months) following administration of the last dose of study vaccines for each subject. See Section 8.4 for instructions on reporting and recording SAEs.

In addition to the above-mentioned reporting requirements and in order to fulfill international reporting obligations, SAEs that are related to study participation (e.g. protocol-mandated procedures, invasive tests, a change from existing therapy) or are

related to a concurrent GSK medication/vaccine or any fatal SAE will be collected and recorded from the time the subject consents to participate in the study until he/she is discharged.

The standard time period for collecting and recording pregnancies will begin at the first receipt of study vaccines and will end 180 days (approximately 6 months) following administration of the last dose of study vaccine. See section 8.4 for instructions on reporting of pregnancies.

The standard time period for collecting and recording of pIMDs will begin at the first receipt of study vaccines will end 180 days (approximately 6 months) following administration of the last dose of study vaccines. See section 8.4 for instructions on reporting of pIMDs.

An overview of the protocol-required reporting periods for adverse events, serious adverse events and pregnancies is given in Table 26.

**Table 26 Reporting periods for adverse events, serious adverse events and pregnancies**

| Study activity                                                                                              | Pre-V1    | V1 | 6 days post-V1 | 27 days post-V1 | V2 | 6 days post V2 | 27 days post-V2 | V3 | 6 days post V3 | Challenge | 29 days post-V3 | 29 days post-challenge | Study Conclusion |
|-------------------------------------------------------------------------------------------------------------|-----------|----|----------------|-----------------|----|----------------|-----------------|----|----------------|-----------|-----------------|------------------------|------------------|
| Study day                                                                                                   | -90 to -1 | 0  | 6              | 27              | 28 | 34             | 55              | 56 | 62             | 77        | 85              | 107                    | 236              |
| Reporting of solicited local and general AEs                                                                |           |    |                |                 |    |                |                 |    |                |           |                 |                        |                  |
| Reporting of unsolicited AEs                                                                                |           |    |                |                 |    |                |                 |    |                |           |                 |                        |                  |
| Reporting of SAEs                                                                                           |           |    |                |                 |    |                |                 |    |                |           |                 |                        |                  |
| Reporting of SAEs related to study participation or GSK concurrent medication/vaccination and any fatal SAE |           |    |                |                 |    |                |                 |    |                |           |                 |                        |                  |
| Reporting of pregnancies                                                                                    |           |    |                |                 |    |                |                 |    |                |           |                 |                        |                  |
| Reporting of pIMDs                                                                                          |           |    |                |                 |    |                |                 |    |                |           |                 |                        |                  |

Pre-V: pre-vaccination; V: vaccination; Post-V: post-vaccination

A post-study AE/SAE is defined as any event that occurs outside of the AE/SAE reporting period defined in [Table 26](#). Investigators are not obligated to actively seek AEs or SAEs in former study participants. However, if the investigator learns of any SAE at any time after a subject has been discharged from the study, and he/she considers the event reasonably related to the investigational product, the investigator will promptly notify the Study Contact for Reporting SAEs.

### **8.3.2. Evaluation of adverse events and serious adverse events**

#### **8.3.2.1. Active questioning to detect adverse events and serious adverse events**

As a consistent method of soliciting AEs, the subject should be asked a non-leading question such as:

*‘Have you felt different in any way since receiving the vaccine or since the previous visit?’*

When an AE/SAE occurs, it is the responsibility of the investigator to review all documentation (e.g. hospital progress notes, laboratory, and diagnostics reports) relative to the event. The investigator will then record all relevant information regarding an AE/SAE on the eCRF or SAE Report screens as applicable. It is not acceptable for the investigator to send photocopies of the subject’s medical records to GSK Biologicals instead of the appropriate completed AE/SAE screens in the eCRF. However, there may be instances when copies of medical records for certain cases are requested by GSK Biologicals, MVI and Crucell. In this instance, all subject identifiers will be blinded on the copies of the medical records prior to submission to GSK Biologicals, MVI and Crucell.

The investigator will attempt to establish a diagnosis pertaining to the event based on signs, symptoms, and/or other clinical information. In such cases, the diagnosis should be documented as the AE/SAE and not the individual signs/symptoms.

**8.3.2.2. Assessment of adverse events****8.3.2.2.1. Assessment of intensity**

Intensity of the following AEs will be assessed as described:

**Table 27 Intensity scales for solicited symptoms**

| Adverse Event                                                                    | Intensity grade | Parameter                                                                           |
|----------------------------------------------------------------------------------|-----------------|-------------------------------------------------------------------------------------|
| Pain at injection site                                                           | 0               | None                                                                                |
|                                                                                  | 1               | Mild: Any pain neither interfering with nor preventing normal every day activities. |
|                                                                                  | 2               | Moderate: Painful when limb is moved and interferes with every day activities.      |
|                                                                                  | 3               | Severe: Significant pain at rest. Prevents normal every day activities.             |
| Redness at injection site                                                        |                 | Record greatest surface diameter in mm                                              |
| Swelling at injection site                                                       |                 | Record greatest surface diameter in mm                                              |
| Fever*                                                                           |                 | Record temperature in °C/°F                                                         |
| Headache                                                                         | 0               | Normal                                                                              |
|                                                                                  | 1               | Mild: Headache that is easily tolerated                                             |
|                                                                                  | 2               | Moderate: Headache that interferes with normal activity                             |
|                                                                                  | 3               | Severe: Headache that prevents normal activity                                      |
| Fatigue                                                                          | 0               | Normal                                                                              |
|                                                                                  | 1               | Mild: Fatigue that is easily tolerated                                              |
|                                                                                  | 2               | Moderate: Fatigue that interferes with normal activity                              |
|                                                                                  | 3               | Severe: Fatigue that prevents normal activity                                       |
| Gastrointestinal symptoms
(nausea, vomiting, diarrhoea and/or abdominal pain) | 0               | Gastrointestinal symptoms normal                                                    |
|                                                                                  | 1               | Mild: Gastrointestinal symptoms that are easily tolerated                           |
|                                                                                  | 2               | Moderate: Gastrointestinal symptoms that interfere with normal activity             |
|                                                                                  | 3               | Severe: Gastrointestinal symptoms that prevent normal activity                      |
| Chills                                                                           | 0               | Normal (no chills)                                                                  |
|                                                                                  | 1               | Feel cold without obvious cause                                                     |
|                                                                                  | 2               | Shivering (controllable, <15 sec)                                                   |
|                                                                                  | 3               | Rigors (uncontrollable shivering >15 sec)                                           |

\*Fever is defined as: axillary/oral/tympanic temperature  $\geq 38.0^{\circ}\text{C}$  ( $100.4^{\circ}\text{F}$ ). The preferred route for recording temperature in this study will be oral.

The maximum intensity of local injection site redness/swelling will be scored at GSK Biologicals as follows:

|   |   |                      |
|---|---|----------------------|
| 0 | : | 0 mm                 |
| 1 | : | > 0 - $\leq$ 50 mm   |
| 2 | : | > 50 - $\leq$ 100 mm |
| 3 | : | > 100 mm             |

The maximum intensity of fever (oral measurement) will be scored at GSK Biologicals as follows:

|   |   |                                     |
|---|---|-------------------------------------|
| 0 | : | < 38.0°C or 100.4°F                 |
| 1 | : | ≥38.0 - < 38.5°C or 100.4 - 101.2°F |
| 2 | : | ≥38.5 - < 39.0°C or 101.2 - 102.1°F |
| 3 | : | ≥ 39.0°C or 102.1°F                 |

The investigator will assess the maximum intensity that occurred over the duration of the event for all other AEs, i.e. unsolicited symptoms, including SAEs reported during the study. The assessment will be based on the investigator's clinical judgement.

The intensity of each AE and SAE recorded in the eCRF or SAE Report screens, as applicable, should be assigned to one of the following categories:

- |              |   |                                                                                                                                                                                                                   |
|--------------|---|-------------------------------------------------------------------------------------------------------------------------------------------------------------------------------------------------------------------|
| 1 (mild)     | = | An AE which is easily tolerated by the subject, causing minimal discomfort and not interfering with everyday activities.                                                                                          |
| 2 (moderate) | = | An AE which is sufficiently discomforting to interfere with normal everyday activities.                                                                                                                           |
| 3 (severe)   | = | An AE which prevents normal, everyday activities

(In adults/adolescents, such an AE would, for example, prevent attendance at work/school and would necessitate the administration of corrective therapy.) |

An AE that is assessed as Grade 3 (severe) should not be confused with a SAE. Grade 3 is a category utilised for rating the intensity of an event; and both AEs and SAEs can be assessed as Grade 3. An event is defined as 'serious' when it meets one of the pre-defined outcomes as described in Section 8.1.2.

Acceptable/normal ranges and toxicity grading for laboratory safety parameters are provided in Table 28.

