### *Individual stopping rules*

In addition to the above stated group holding rules, stopping rules for individual subjects will apply (i.e., indications to withdraw individuals from further vaccinations). These will apply to Cohort A, B and C. The PI will have the responsibility to withdraw from further vaccination individual study participants who present at least one of the following stopping rules for individual subjects:

- Local reactions: upon investigator discretion.

- Systemic solicited adverse events:
  - the subject develops a Grade 3 systemic solicited adverse event beginning within 2 days after vaccination (day of vaccination and one subsequent day) and persisting at Grade 3 for > 2 consecutive days.
- Unsolicited adverse events
  - the subject has any Grade 3 adverse event considered related to vaccination, persisting at Grade 3 for >2 consecutive days.
  - the subject has a serious adverse event considered related to vaccination.
  - the subject has an acute allergic reaction or anaphylactic shock following the administration of vaccine investigational product.
- Laboratory adverse events
  - the subject has any Grade 3 laboratory adverse event considered related to vaccination.
  - the subject, excluding menstruating female, develops hematuria considered related to vaccination.

The PI may, using discretion, ask for the study to be placed on hold and an SMC meeting to be held for any single event or combination of multiple events which, in professional opinion, jeopardize the safety of the subjects or the reliability of the data.

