**Table 24 Solicited general adverse events**

|                                        |
|----------------------------------------|
| Fatigue                                |
| Fever                                  |
| Gastrointestinal symptoms † |
| Headache                               |
| Chills                                 |

†Gastrointestinal symptoms include nausea, vomiting, diarrhoea and/or abdominal pain.

Note: Temperature will be recorded once per day. Should additional temperature measurements be performed, the highest temperature will be recorded in the eCRF.

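### Fever scale: the Fahrenheit lower limits for Grades 2 and 3 are each printed 0.1°F too low, so a reading of 102.1°F (38.94°C) can be graded 3 although it is Grade 2 in Celsius

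*Protocol*

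**What the plan says.** The fever scale stands below Table 27 in Protocol Section 8.3.2.2.1 and is introduced with "The maximum intensity of fever (oral measurement) will be scored at GSK Biologicals as follows". Its bands are:

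- Grade 1: "≥38.0 - < 38.5°C or 100.4 - 101.2°F"
- Grade 2: "≥38.5 - < 39.0°C or 101.2 - 102.1°F"
- Grade 3: "≥ 39.0°C or 102.1°F"

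Table 27 itself asks the site only for the reading, in either unit: "Record temperature in °C/°F". The note to Table 24 calls for one temperature per day and adds: "Should additional temperature measurements be performed, the highest temperature will be recorded in the eCRF".

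The Grade 3 limit is used in four places:

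- the primary safety endpoints (Synopsis), which count Grade 3 solicited general events;
- the rule for moving from dose 2 to dose 3 (Section 5.4.4.1.2);
- the Cohort A holding rules (Section 5.4.4.1.3);
- the individual stopping rules (same section), which state "The PI will have the responsibility to withdraw from further vaccination individual study participants". One trigger is that "the subject develops a Grade 3 systemic solicited adverse event beginning within 2 days after vaccination" and stays at Grade 3 for more than two consecutive days.

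**The concern.** The figures 101.2°F and 102.1°F are each printed twice, once as the top of a grade and again as the bottom of the next. As inclusive upper limits they are right: to one decimal they are the last Fahrenheit values below 38.5°C and 39.0°C. As lower limits they are wrong, because the Celsius limits beside them convert to 101.3°F and 102.2°F.

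Fahrenheit is a live unit here. Table 27 allows it, the trial is run entirely in the United States (Section 4.2), and no sentence says that Celsius prevails or that readings are converted before grading. A reading of exactly 102.1°F could therefore count as Grade 3 in the solicited-event tables, or be taken as Grade 3 when the principal investigator decides whether a volunteer must stop vaccination. This is the only fever scale in the protocol, so the investigator has no other to fall back on.

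**Working it through.** **Inputs.** The Celsius and Fahrenheit limits come from the fever scale in Section 8.3.2.2.1. The Cohort A group size of 28 comes from Section 5.4.3. The threshold of more than 25% comes from Sections 5.4.4.1.2 and 5.4.4.1.3.

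**Step 1: convert the Celsius lower limits, F = C × 1.8 + 32.**

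| Lower limit of | °C | Converted °F | Printed °F | Printed minus converted |
|---|---|---|---|---|
| Grade 1 | 38.0 | 100.4 | 100.4 | 0 |
| Grade 2 | 38.5 | 101.3 | 101.2 | −0.1 |
| Grade 3 | 39.0 | 102.2 | 102.1 | −0.1 |

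All three conversions are exact to one decimal, so rounding does not explain the gap.

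**Step 2: convert the disputed readings back, C = (F − 32) / 1.8.**

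- (101.2 − 32) / 1.8 = 38.44°C, below 38.5, so Grade 1 in Celsius.
- (102.1 − 32) / 1.8 = 38.94°C, below 39.0, so Grade 2 in Celsius.

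**Step 3: grade every 0.1°F reading from 100.3 to 102.3 both ways.** The ≥ and < signs stand only before the Celsius figures, so the Fahrenheit bands can be read in two ways.

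| Reading | Celsius grade | Fahrenheit bands, both ends included | Fahrenheit bands, Celsius signs carried across |
|---|---|---|---|
| 101.2°F | 1 | 1 and 2 | 2 |
| 102.1°F | 2 | 2 and 3 | 3 |

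From 100.4°F upwards, these are the only two readings on which the units disagree, and they disagree on both interpretations.

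**Step 4: what it takes to change a decision.**

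- *Individual rule.* If days are counted by the single daily maximum, more than two consecutive days means at least three consecutive values. The misprint decides a case only if the run starts on day 0 or day 1, every value is at least 102.1°F, and at least one value needed for the run is exactly 102.1°F.
- *Group rules.* With 28 ARR doses, 7/28 = 25.0% does not exceed 25% and 8/28 = 28.6% does, so 8 are needed. With 24 to 27 doses, 7 are needed: 6/24 = 25.0% and 6/27 = 22.2% do not meet the rule, while 7/24 = 29.2% and 7/27 = 25.9% do. Each event must also persist as above, and the systemic holding rule requires it to be judged related to vaccination.

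**Step 5: check the correction.** With Grade 1 at 100.4-101.2°F, Grade 2 at 101.3-102.1°F and Grade 3 from 102.2°F, every reading from 100.3 to 102.3°F falls in exactly one grade and agrees with Celsius.

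**The case against.** There are four arguments on the other side.

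**The overlap depends on how the table is read.** Grade 0 is printed with 100.4°F as its limit, and that makes sense only if the sign before the Celsius figure also applies to the Fahrenheit one. If so, no reading belongs to two grades. This is a fair point, and it makes the overlap one of two possible readings. It does not rescue the limits: 102.1°F is then plainly Grade 3 by the Fahrenheit band and Grade 2 by the Celsius band.

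**Celsius looks like the primary scale.** Fever is defined in Celsius first throughout, and a trained grader would probably follow the signed Celsius bands. That is reasonable, but it is an inference, since the protocol does not say so.

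**Central scoring protects the endpoint.** One scorer applying one rule to both arms makes differential misgrading unlikely. This stands and limits the effect on the safety tables. It helps less with the individual rule: the investigator is responsible for withdrawal, and the protocol does not say who grades the fever for that purpose.

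**The practical effect is negligible.** Fever is one of five solicited general events in Table 24. The persistence condition is demanding, and Section 5.6.3.9 supplies digital thermometers without giving their unit or resolution. All of this stands. It sets the weight of the point but does not make the printed figures right.

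**Conclusion.** The concern holds as a minor correction. Both Fahrenheit lower limits are 0.1°F too low, and this follows from exact conversion.

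The size assumes thermometers that read in Fahrenheit to one decimal; readings taken in Celsius are unaffected. On that assumption two readings are affected, and only 102.1°F alters Grade 3 status. The individual-rule result further assumes that days are counted by the recorded daily maximum.

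The misgrading runs only upwards, which is cautious for stopping. A changed group decision is very unlikely. An individual withdrawal could turn on the error only in the narrow run of readings described above. The point is still worth correcting because the wrong figure is an operating threshold for a safety endpoint and for withdrawal from vaccination.

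**What to change.** Correct the two lower limits in Section 8.3.2.2.1 and write the Fahrenheit bands as Grade 1 100.4-101.2°F, Grade 2 101.3-102.1°F and Grade 3 102.2°F or above.

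Alternatively, add one sentence stating that every temperature is converted to Celsius before it is graded, whether by the sponsor for analysis or by the principal investigator for the individual stopping rule.

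The cost is two figures or one sentence. Neither option needs new data or changes any visit.
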